### Data collection

Data collection time points are outlined in Fig. 1. Study personnel will assess the subject’s pain score and vital signs at baseline and again at eight predetermined intervals using the 11-point NRS (Fig. 3). Adverse events will be monitored throughout the follow-up period. Additionally, subject satisfaction with their care and total amount of required analgesic medications will be assessed at the conclusion of the study for each participant. Baseline demographic characteristics and information on mechanism of injuries will also be gathered at the time of enrollment. As the population being evaluated will be followed-up for only 24 h at a single study site and will have substantial physical trauma, it is likely that losses to follow-up through discharge prior to 24 h or patients leaving against medical advice will be minimal.

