### Statistical analysis

#### Sample size

The sample size for this study uses a framework of an equivalency trial with parenteral morphine as the standard of care versus morphine with RA as the novel treatment. The new modality is further divided into two arms of RA: FICB and US-guided FNB. For the purpose of this study, a clinically important effect size was defined as a 20 % change in the primary outcome of the SPID. Based on this assumption, a sample size of 63 patients per arm provides 90 % power to show equivalence between each group (e.g. RA administered via FICB as compared to standard care or RA performed using a FNB versus standard care), assuming a standard deviation (SD) up to 20, a difference between the SPID group means of 0 and an equivalence of 13, at a 2.5 % significance level (one-sided). Allowing for 10 % attrition, the sample size is 69 patients per arm, with 207 participants in total.

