#### Outcome analysis and reporting

The primary outcome variable, SPID, will be calculated using the pain-intensity difference (PID) at each time point outlined in Fig. 1, which is the difference between the patient’s pain level at that time on a standard 0–10 scale and the patient’s baseline pain level [25]. The SPID will be calculated by summing the pain intensity difference (PID) at each of the study time points, weighted by the amount of time since the prior assessment; this approximates the area under the curve for PID over time. SPID will also be reported as a percentage of maximum possible SPID.

Baseline patient characteristics and outcome measures will be reported using means and standard deviations, medians and ranges, or proportions as appropriate. Analysis of variance (ANOVA) and Student’s *t* test will be employed to determine differences between study arms for continuous measures, including the primary outcome of SPID, and the Fisher’s exact test will be used for differences in categorical variables. Two-way ANOVA testing with repeated measures in one factor (time) will be performed to compare the effect of treatment arm over time on pain-intensity measures.

Missing data will be handled using multiple-imputation models and standard error uncertainty estimates in which missing data will be replaced using summary outcomes from participants with complete data for each variable of interest. To assess the robustness of the models, sensitivity analyses will be performed in which the primary outcome will be compared with and without those lost to follow-up included and assumed to have the mean SPID correlating to the allocation arm of initial randomization.

Prior to trial initiation, a statistical analysis plan with formalized procedural protocols will be created. Analyses will be performed using STATA 13.0 (StataCorp LP, College Station, TX, USA). A *p* value of less than 0.05 will be considered significant for all analyses. All data analyses will be coded on program files to allow independent reproduction of analyses.

Reporting of outcomes will follow the most up-to-date Consolidated Standards of Reporting Trials (CONSORT) guidelines as well as the extensions to equivalence trials; and to nonpharmacological interventions. The collected data set will also be made available in conjunction with the associated trial report.

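### Giving lost patients their own arm's mean SPID reproduces the complete-case difference with a falsely small standard error, so it cannot test robustness; the primary missing-data sentence also contradicts itself

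*Protocol article*

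**What the plan says.** All the rules are in the protocol article, under Outcome analysis and reporting.

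- **Primary rule, opening:** "Missing data will be handled using multiple-imputation models and standard error uncertainty estimates".
- **Primary rule, rest of the same sentence:** in these models "missing data will be replaced using summary outcomes from participants with complete data for each variable of interest".
- **Sensitivity analysis:** its stated purpose is to assess how robust the models are. For this, "the primary outcome will be compared with and without those lost to follow-up included", and those lost are "assumed to have the mean SPID correlating to the allocation arm of initial randomization".
- **Test:** ANOVA and "Student’s *t* test will be employed to determine differences between study arms for continuous measures, including the primary outcome of SPID".

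The Sample size section plans for 10 % attrition, giving 69 randomized per arm. The Data collection section is more optimistic and expects that "losses to follow-up through discharge prior to 24 h or patients leaving against medical advice will be minimal". A separate statistical analysis plan is promised before the trial starts.

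**The concern.** A sensitivity analysis for missing data is useful only if its answer could differ when the missing patients fared differently from those observed. The stated rule fixes the missing patients at the average of the observed patients in their arm. It therefore assumes the very thing that should be tested.

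It also treats invented values as real observations, which makes the SE too small. The trial is declared and sized as an equivalence trial, where a confidence interval that is falsely narrow favours the conclusion sought.

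The primary rule raises a second problem. Multiple imputation draws several plausible values for each gap so that the uncertainty reaches the SE. Replacing a gap by a summary of the completers does not do that. The two halves of the sentence describe different procedures, and a programmer could follow either.

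**Working it through.** **Inputs (protocol article).** From Sample size: SD 20, true difference 0, equivalence margin 13, one-sided 2.5 %, 90 % power, 63 per arm, 10 % attrition, 69 randomized per arm. From Outcome analysis and reporting: the test and the imputation rules. Observed per arm at 10 % loss: 69 × 0.9 = 62.1, taken as r = 62 of n = 69.

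**1. The plan's own figure.** The article says that "a sample size of 63 patients per arm provides 90 % power to show equivalence between each group". With two one-sided tests, n = 2 × [20 × (1.960 + 1.645) / 13]² = 61.5, so 62 per arm. At 63 per arm, power is 0.909 (normal) or 0.904 (simulation with the t distribution). The stated 63 is reproduced closely enough. For attrition, 63 × 1.10 = 69.3, against the stated 69.

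**2. The estimate under the sensitivity rule.** Let m be the mean of the r observed patients in an arm. After n − r values equal to m are added, the mean is [r × m + (n − r) × m] / n = m. This holds in every arm, so the difference between arms equals the complete-case difference exactly, whatever the amount or cause of loss.

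**3. The SE under the sensitivity rule.** The added values contribute nothing to the sum of squares, so the variance estimate is multiplied by (r − 1)/(n − 1). The apparent sample size rises from r to n. Hence

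SE ratio = √[r(r − 1) / (n(n − 1))] = √[62 × 61 / (69 × 68)] = √(3782 / 4692) = 0.898.

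The complete-case SE is 20 × √(2/62) = 3.59. After arm-mean imputation it is 3.59 × 0.898 = 3.23.

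**4. Consequences.** These assume normal data and losses unrelated to outcome, so that the complete-case analysis is valid. The second row assumes a loss of 3 of 69 per arm (4.3 %), to show a smaller case.

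| Observed per arm | SE ratio | 95 % half-width, complete case → imputed | Actual coverage | One-sided error at margin | Apparent power at true difference 0 |
|---|---|---|---|---|---|
| 62 of 69 | 0.898 | 7.11 → 6.38 | 92.2 % | 3.9 % (nominal 2.5 %) | 0.897 → 0.933 |
| 66 of 69 | 0.956 | 6.89 → 6.58 | 93.9 % | 3.0 % (nominal 2.5 %) | 0.919 → 0.933 |

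The error at the margin is the tail probability of the t distribution with 2(r − 1) degrees of freedom; a simulation of 1,000,000 draws agrees (3.9 % and 3.0 %).

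**5. What an informative check could show.** Suppose, as an assumption, that the 7 patients lost from one arm differ from its completers by one SD (20). That arm's mean moves by 7/69 × 20 = 2.0 SPID units. With an observed difference of 0, the room between interval and margin is 13 − 7.11 = 5.89, so the shift uses about a third of it. The planned analysis would report a shift of exactly 0.

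**6. The primary sentence read literally.** One summary value per gap has no between-imputation variability.

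- If the summary is the arm mean, the SE shrinks as in step 3.
- If it is the mean over all arms, the estimated difference is multiplied by about 62/69 = 0.90, which pulls it towards zero and so towards equivalence.

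The text does not say which summary is meant.

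**The case against.** The strongest defence concerns the primary rule. A reader might infer that the trial simply uses mean replacement under the name of multiple imputation, and that the primary p value and interval are therefore too optimistic. The article does not support that. The same sentence names multiple-imputation models and a treatment of SE uncertainty. It never says that the summary is a mean, nor whether it is taken by arm. It may be a loose description of draws from the completers' distribution. This defence stands: what can be shown is a contradiction, with consequences that depend on the reading.

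Other stronger readings also fail:

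- **That both rules replace a whole SPID.** Only the sensitivity rule names SPID. The primary rule speaks of each variable, which can include single pain scores.
- **That the check is certain to confirm the primary result.** The estimate cannot move from the complete-case value, but the narrower interval can change a verdict. Both estimates may also differ from a proper multiple-imputation result.
- **That losses depend on pain.** The article names early discharge and leaving against advice, but does not link either to pain. A link is plausible, not documented.
- **That losses will be large.** Nothing in the article suggests more than 10 %, and that is an allowance in the sample size.

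It can also be said that imputation details belong in the analysis plan. That is true of details left out, and their absence is no finding. The arm-mean rule and the summary-outcome clause are stated, and the analysis plan would inherit them.

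**Conclusion.** The point on the sensitivity analysis holds in full, because it is algebra and does not depend on how much data are lost. The analysis tests no departure from missing at random and cannot do the job the article gives it. Its numerical harm is moderate at the planned 10 % attrition: an SE about 10 % too small, and an error rate at the margin of 3.9 % for a nominal 2.5 %. It is small if losses are as few as the article expects. These figures rest on equal loss in both arms, normal data and loss unrelated to outcome. The SE ratio itself does not depend on the value of the SD.

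The point on the primary rule holds only as an internal contradiction. Read literally it is single-value replacement, with either an SE that is too small or a difference shrunk to about 0.90 of its size. Whether the primary result would be affected cannot be settled from the article.

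**What to change.** 1. **Primary rule.** Delete the clause on replacement by summary outcomes. State that missing pain scores are multiply imputed by arm from the baseline score and the scores at the other time points, that SPID is derived in each imputed data set, and that results are combined by Rubin's rules. This also uses the scores that a patient gave before leaving.
2. **Sensitivity analysis.** Replace the arm-mean rule by a delta-adjusted or tipping-point analysis, in which imputed scores are shifted progressively and separately by arm until the conclusion changes.
3. **Complete cases.** Keep the complete-case analysis as a secondary comparison.

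The cost is some analysis code and slightly wider intervals. Sample size and data collection do not change. The analysis plan is still to be written before the trial starts, so the correction can be made there and in the protocol.

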### Safety monitoring

An independent Data Safety Monitoring Board (DSMB) will review participant safety and efficacy of therapies. The DSMB will be able to recommend modification if there is concern over undue risk stemming from adverse events or other safety concerns. The DSMB will be identified prior to the start of the study and will be activated when the trial commences.

All research methods will be specified in Standard Operating Procedures (SOP). An internal study monitor will be integrated into the research team to assess protocol adherence during data collection. Additionally, the RAPID trial coordinators will be in the field for the study to ensure safe and ethical conduct.

All patients who are enrolled in the trial will be monitored for adverse events. Monitoring will occur via standardized assessments at predefined time points throughout the 24-h follow-up period (Fig. 1). Continuous monitoring by study personnel will be undertaken for a 30-min period following the administration of any study treatment medication to assess for immediate serious adverse events (SAE).

For the purpose of this study, SAE includes hemorrhage, allergic reaction, anaphylaxis, hypotension, respiratory depression, compartment syndrome, intraneural injection, local anesthetic systemic toxicity (LAST), or death. With the occurrence of any SAE, study personnel will initiate immediate treatment in conjunction with the participant’s primary health care team. The onsite coordinator, principle investigators, and DSMB will be made aware within 24 h of any SAE.

### Ethical approval

The RAPID trial has received ethical approval from the MSF Ethical Review Board (Reference number: 1524). The trial will be conducted in accordance with the Declaration of Helsinki, as well as the International Conference on Harmonization (ICH). Collected data will not be linked to any individual or personal identifiers. Confidentiality will be maintained at all levels of data management.

Within 72 h of the earthquake, the research team will attempt to identify an ethics committee in the country in which the disaster occurred, which will be given the opportunity to review the trial protocol and prior ethical approvals and recommend any changes deemed necessary. In the absence of a local ethics committee, the research team will attempt to contact the appropriate department in the local MoH to obtain authorization for the study prior to beginning recruitment at the MSF field hospital. Recruitment will not begin until these local approvals have been obtained. In addition, all attempts will be made to recruit local coinvestigators to support the management of the research study.

## Discussion

Earthquakes cause the greatest burden of injuries among all natural disasters globally [1, 2]. Studies of injury patterns from earthquakes show that approximately half of all patients sustain lower extremity injuries [3–6], and that pain management for these victims is often inadequate [11–13]. The shortage of sufficient narcotic medications in LMIC settings, where the majority of earthquake injuries occur, further compounds this problem [16].

While there are reports on the use of RA for pain control in disaster settings, there have been no controlled studies evaluating whether RA has added benefit over narcotics alone [13, 29]. This trial will rigorously evaluate the role of RA and also be the first to assess if a focused training for generalist health care providers is sufficient to effectively perform RA in the aftermath of a major disaster. Given the novelty of this particular research study, as well as the approach of performing an RCT in the aftermath of a major disaster, the RAPID trial has the potential to transform the management of pain in earthquake settings as well as research in acute disaster settings.

The utility of RA in pain management of lower extremity trauma in high-income country hospitals is well-described [24–26]. However, the injury patterns and clinical parameters of this population are not representative of a post-earthquake setting, where resources are often scarce and injuries more complex. Although there are anecdotal reports on the use of RA from contemporary earthquake events [13, 28, 29], this data is limited and equipoise exists as to whether RA improves pain control for lower extremity injuries of disaster victims. The RAPID study will utilize a blinded RCT equivalence design to address this patient-centered question. Although a nonrandomized observational study would be less resource and methodologically intensive, such a design would likely suffer from confounding as patients with more serious injuries, who are more likely to experience adverse events and less likely to achieve adequate pain control, would have a higher probability of receiving RA. Additionally, as the RAPID study outcomes include assessments of pain, blinding is crucial in order to avoid bias due to the placebo effect and, therefore, necessitates a controlled trial design.

If the RAPID trial demonstrates the effectiveness of RA, the findings will provide high-quality evidence to inform the management of traumatic injuries in disaster settings. Studies conducted after contemporary earthquakes report oligioanalgesia, both for patients with severe injuries and for those undergoing painful procedures [11–13, 28]. RA may help reduce pain and suffering of the large numbers of individuals injured in major earthquakes annually, while also aiding in the provision of more definitive treatments of injuries through fracture and wound management. Beyond earthquakes, the medical literature on conflict-associated injuries also demonstrates high rates of lower limb trauma, which suggests possible application of the RAPID findings beyond earthquake settings to those injuries sustained during other types of humanitarian emergencies [17].

The training of international and local generalist health care providers as proceduralists in the trial will enhance the external validity of the findings, as the likelihood of having access to a large body of specialists trained in RA techniques in a LMIC disaster setting is low. In addition, RA can be performed with local anesthetics that have a nominal cost per dose to administer, making it a very cost-effective intervention in even the most resource-limited settings. If the hypothesis of this trial is proven, the use of regional anesthesia for painful injuries after disasters may serve in subsequent disasters to be both a very cost-effective and locally appropriate method to improve pain management and reduce long-term morbidity and post-injury disability [12, 17, 38, 39].

To date, there have been no studies anywhere in the world evaluating the effectiveness, safety, or acceptability of RA in the aftermath of a major earthquake. Indeed, there have been no RCTs evaluating any acute patient-centered medical intervention in the aftermath of a major earthquake. Therefore, beyond addressing the immediate need for improved pain management in these settings, the RAPID study is also pioneering new methodologies in humanitarian and disaster research. Although the evidence base for humanitarian response is replete with retrospective studies, there is a dearth of high-level evidence from prospective trials to inform the care of disaster victims [40]. This deficit results in the use of data extrapolated from nondisaster populations and consensus opinions for developing treatment recommendations in disaster settings [14]. As such, execution of a rigorous RCT in an acute disaster setting will serve to improve the current evidence base, future research activities, and subsequent humanitarian response guidelines.

With the high burden of disease, consistent patterns of injuries and inadequate pain management documented in earthquake settings, new interventions to address this substantial global health problem are needed. The RAPID study will be the first prospective RCT to evaluate whether RA administered by generalist health care providers, either with or without US-guidance, can safely and effectively reduce suffering and pain from earthquake-related lower limb injuries in a disaster setting.

### Trial status

Ethical approval for the study has been obtained from the MSF Ethical Review Board and 12 study personnel from MSF have been trained in the trial SOP. The study will commence after a major earthquake meeting the criteria outlined above occurs in a LMIC to which MSF has been asked by local government to deploy a field hospital.

## Abbreviations

CRED: Center for Research on the Epidemiology of Disasters
DSMB: Data Safety Monitoring Board
GCP: Good Clinical Practices
ICH: International Conference on Harmonization
LAST: Local Anesthetic Systemic Toxicity
LMIC: Low- and middle-income country
MoH: Ministry of Health
MSF: Médecins Sans Frontières
NRS: Numerical Rating Scale
PID: Pain intensity difference
RA: Regional anesthesia
RCT: Randomized controlled trial
SAE: Serious adverse events
SPID: Summed pain intensity difference
US: Ultrasound
WHO: World Health Organization
